### Data of withdrawn participants

Data will be handled in accordance with Art 9. ClinO [26], which we quote here in full from the relevant section:

*«Widerruft die betroffene Person ihre Einwilligung, so sind das biologische Material und die gesundheitsbezogenen Personendaten nach Abschluss der Datenauswertung zu anonymisieren».*

### Handling of Drop outs

Should a patient withdraw prior to completion of the second examination, that patient will be replaced and recruitment will continue until 100 patients have been recruited.

For patients who withdraw consent at any point, the data up to the time point of withdrawal will be used.

# STUDY INTERVENTION

## Identity of Investigational Products (treatment / medical device)

For a full description of the two radiopharmaceuticals under investigation, we refer to the “Fachinformation” (Appendix A).

### Experimental Intervention (treatment / medical device)

No experimental treatment is used. Routinely used radiopharmaceuticals are compared.

### Control Intervention (standard/routine/comparator treatment / medical device)

Intra-individual comparison of both radiopharmaceuticals, as described previously.

### Packaging, Labelling and Supply (re-supply)

Labelling is in accordance with good clinical practice and the requirements of the federal ministry of health and were approved by SwissMedic. This study is open-label in design.

### Storage Conditions

Storage of the radiopharmaceuticals is in accordance with good clinical practice.

## Administration of experimental and control interventions

### Experimental Intervention

Non applicable.

### Control Intervention

For the rationale behind our dose concept, we refer to §3.5 “Dose Rationale”. Radiation exposure to humans is as outlined in the submission to the FOPH (in parallel to this application, and included in Appendix B). For reference, we recapitulate the radiation exposure here:

Estimate of the Radiation Exposure

• ^68^Ga-PSMA-11: 150 ± 15% MBq applied activity corresponds to a maximum of 3.5 mSv for the radiopharmaceutical, with 5 mSv for the first-low dose CT (5mSv) = total 8.5 mSv

• ^18^F-PSMA-1007: 300 ± 15% MBq applied activity corresponds to 6.6 mSV for the radiopharmaceutical, with 5 mSv the first low-dose-CT = total 11.6 mSv

For the n=10 patients undergoing dynamic (parametric) acquisitions, the additional radiation dose associated with the extra low dose CT scan for attenuation correction is 1mSv, resulting in estimated radiation exposures of 9.5 and 12.6 mSv, respectively.

The additional radiation dose incurred by participation in the study (given the fact that one of the examinations is clinically indicated and is routinely performed, irrespective of whether the individual is in the study or not) is therefore below 12mSv. This is below the 20 mSv limit mandated by the FOPH.

## Dose / Device modifications

No modification of the dose or scan protocol is permitted.

## Compliance with study intervention

Directly observed administration of the radiopharmaceutical ensures compliance with the intervention.

## Data Collection and Follow-up for withdrawn participants

Patients withdrawn due to withdrawn consent will not be followed up. Data collected up until date of withdrawal will still be used. Reasons for withdrawal will be recorded on the CRF (Appendix C).

## Trial specific preventive measures

No specific preventative measures are required for this study.

## Concomitant Interventions (treatments)

No concomitant interventions are anticipated for this study.

## Study Drug / Medical Device Accountability

Accountability of these routinely used radiopharmaceuticals is in accordance with routine clinical practice. The radiopharmaceuticals as clinically routinely used radiopharmaceuticals will be taken from clinical stock and accounted for using established clinical accountability logs. [name] as principal investigator is ultimately responsible for the adherence to good clinical practice.

## Return or Destruction of Study Drug / Medical Device

Surplus substance will be destroyed in accordance with routine clinical practice.

# STUDY ASSESSMENTS

## Study flow chart(s) / table of study procedures and assessments

### Study Procedures

¨

[figure not shown]

[figure not shown]

### Study Calendar

This is shown in section 1.1.1 “study calendar”

## Assessments of outcomes

The primary and secondary outcomes are listed in §5.

### Assessment of primary outcome

Six physicians will read the scans independently of each other. As outlined above in “imaging procedures” (section 6.1.2), the sponsor will provide each reader with a list of scans with a unique identifier, which allows the reader to obtain the scans in a blinded, coded and randomised fashion. The readers will be blinded to all demographic details. The sponsor will randomise the order of the scans, so that scans are not read sequentially. The readers will record the lesion radiotracer uptake and background as previously described in 6.1.2

### Assessment of secondary outcomes

Tumour to background ratio will be compared for both tracers, as described previously in this protocol.

Confirmation for lesions will only be available where the patient’s condition dictates further clinical follow up, such as repeat imaging, or where histology is performed. This data will be collected, and as a secondary explorative outcome, follow-up for lesions rated as pathological will be done by composite follow-up standard of imaging, PSA and histology up to 6 months’ follow up. It is important to note that the performance of histology, further imaging or treatment is not a study specific intervention and is performed when considered clinically appropriate by the patient’s treating physician.

For n=10 individuals parametric imaging will be performed using standard parametric imaging analysis software with only descriptive statistics.

### Assessment of other outcomes of interest

In a second round of tumour classification, two readers will classify each lesion on a lesion-specific approach in consensus (this cannot be done as a primary outcome with multiple readers, owing to the lack of a coordinate system by which multiple lesions can easily be referred to). Lesions classified as benign, equivocal or pathological will be referenced against further imaging, histology or post-treatment response to focal therapy, which will allow an exploration of the lesion-based performance of the tracers.

### Assessment of safety outcomes

Any adverse events will be recorded. Tolerability of the radiotracer will be followed up 48 hours following administration of the radiotracer by the study nurse, who will have access to a physician should any questions arise. Any AE will be assessed by a physician-investigator.

9.2.4.1 Adverse events

Any adverse event will be recorded in the individual’s clinical notes as per routine clinical usage: time of onset, duration of event, type of event, symptoms, actions taken, time to resolution, assessment of intensity. The results of any root-cause-analysis will be recorded.

Normal routine clinical procedures will be in place for the avoidance of errors in radiopharmaceutical dose and route of administration (each dose will be checked for quality in accordance with routine clinical procedures). Each dose will be double checked by two technologists for dosimetry and route of application as per clinical routine. All doses are recorded in the patient notes and the electronic radiology information system (RIS).

Reporting of Adverse events:

Reported adverse events will be recorded and classified and quantified according to the common terminology criteria for adverse events (CTCAE Version 5.0). Such data will be reported in the trial.

9.2.4.2 Laboratory parameters

Beyond those routinely provided by the referrer, no additional laboratory parameters will be obtained in this study.

9.2.4.3 Vital signs

Weight and height at the time of examination will be recorded as per clinical routine.

### Assessments in participants who prematurely stop the study

Patients who do not undergo a second scan due to an AE will be followed up as routine.

## Procedures at each visit

The study design calls for the patients to be randomised prior to the first examination. Therefore, following clinical referral, patients will be screened for eligibility. If eligible, patients are contacted and provided with the study information. If the patient agrees, following discussion with an investigator, to participate, a consent form will be provided for the patient to sign and return to us.

Patients are then randomised to group A or B and the first clinically indicated exam is scheduled. Should the patient refuse participation or withdraw his consent, the patient will receive the examination with one of the two tracers according to availability. Such a routine examination could occur with either radiotracer, both of which are routinely used both at our centre and throughout Western Europe, and both of which are approved for use in Switzerland.

The patient will have time for reflection between receiving study information and receiving the first examination (min 24hrs). A second opportunity will occur to discuss the examination prior to the second (study-specific) examination.

### Initial (clinically routine, non-study specific) Examination

The individual will be interviewed by an investigator and the patient’s formal inclusion in the study is confirmed. The first clinically routine and non-study specific examination is performed.

Patients will then be invited to return for the second examination.

### Second (study specific) Examination

The patient will return for the second examination. No further patient visits are required. The overall process is outlined in the following figure:

[figure not shown]

# SAFETY

## Drug studies

All adverse events (AEs) and all serious adverse events (SAEs) are collected, fully investigated and documented in source documents and case report forms (CRF) up until the follow up 48h post the second scan.

### Definition and assessment of (serious) adverse events and other safety related events

An **Adverse Event (AE)** is any untoward medical occurrence in a patient or a clinical investigation participant administered a pharmaceutical product and which does not necessarily have a causal relationship with the study procedure. An AE can therefore be any unfavourable and unintended sign (including an abnormal laboratory finding), symptom, or disease temporally associated with the use of a medicinal (investigational) product, whether or not related to the medicinal (investigational) product.

A **Serious Adverse Event (SAE)** is classified as any untoward medical occurrence that:

- results in death,
- is life-threatening,
- requires in-patient hospitalization or prolongation of existing hospitalisation,
- results in persistent or significant disability/incapacity, or
- is a congenital anomaly/birth defect.

In addition, important medical events that may not be immediately life-threatening or result in death, or require hospitalisation, but may jeopardise the patient or may require intervention to prevent one of the other outcomes listed above should also usually be considered serious.

Examples of such events are intensive treatment in an emergency room or at home for allergic bronchospasm, blood dyscrasias or convulsions that do not result in hospitalisation, or development of drug dependency or drug abuse.

SAEs should be followed until resolution or stabilisation. Participants with ongoing SAEs at study termination (including the safety visit) will be further followed up until recovery or until stabilisation of the disease after termination.

*Assessment of Causality*

Both Investigator and Sponsor make a causality assessment of the event to the study drug, based on the criteria listed in the ICH E2A guidelines:

| Relationship | Description |
| --- | --- |
| Definitely | Temporal relationship  Improvement after dechallenge*  Recurrence after rechallenge  (or other proof of drug cause) |
| Probably | Temporal relationship  Improvement after dechallenge  No other cause evident |
| Possibly | Temporal relationship  Other cause possible |
| Unlikely | Any assessable reaction that does not fulfil the above conditions |
| Not related | Causal relationship can be ruled out |
| *Improvement after dechallenge only taken into consideration if applicable to reaction | |

*Unexpected Adverse Drug Reactions*

An “unexpected” adverse drug reaction is an adverse reaction, the nature or severity of which is not consistent with the applicable product information (“Fachinformation” – Appendix A).

*Suspected Unexpected Serious Adverse Reactions (SUSARs)*

The Sponsor-Investigator evaluates any SAE that has been reported regarding seriousness, causality and expectedness. If the event is related to the investigational product and is both serious and unexpected, it is classified as a SUSAR.

*Assessment of Severity*

The severity grading scale used will be the “Common Terminology Criteria for Adverse Events CTCAE Version 5.0”.

### Reporting of serious adverse events (SAEs) and other safety related events

*Reporting of SAEs*

All SAEs must be reported immediately and within a maximum of 24 hours to the Sponsor of the study. The Sponsor will re-evaluate the SAE and return the form to the site.

SAEs resulting in death are reported to the Ethics Committee via BASEC within 7 days.

*Reporting of SUSARs*

A SUSAR needs to be reported to the Ethics Committee via BASEC and to Swissmedic for this category C study (via Sponsor) within 7 days, if the event is fatal, or within 15 days (all other events).

*Reporting of Safety Signals*

All suspected new risks and relevant new aspects of known adverse reactions that require safety-related measures, i.e. so called safety signals, must be reported to the Sponsor within 24 hours. The Sponsor must report the safety signal within 7 days to the Ethics Committee via BASEC and to Swissmedic (category C study).

*Reporting and Handling of Pregnancies*

Not applicable – only male subjects are included in this study.

*Periodic reporting of safety*

A final safety report on completion of the study will be reported to the competent authorities (CEC, Swissmedic).

An annual safety report is submitted once a year to the local Ethics Committee and to Swissmedic in this category C study via the Sponsor.

The FOPH will be furnished with a final report within one year following termination of the study regarding all aspects of radiation protection, in accordance with ClinO Art. 44.

### Follow up of (Serious) Adverse Events

Participants with ongoing SAEs at the 48h follow-up will be followed up until recovery or until stabilisation of the disease after termination. Vital signs, any laboratory values obtained and the clinical condition of the patient will be recorded in the patient’s clinical notes. In cases of loss to follow up, the patient’s general practitioner will be contacted.

## Medical Device Category C studies

Section does not apply.

## Medical Device Category A studies

Section does not apply.

## Assessment, notification and reporting on the use of radiation sources

Under consideration of the potential diagnostic benefit to be gained from examination with the additional radiopharmaceutical [27], and in accordance with article 45 of the Radiological Protection Ordinance of 26 April 2017 (subsection 2), the effective dose incurred by participation in this trial falls below 20mSv.

If the permitted dose guidance value is exceeded at any time, the investigator notifies the Ethics Committee via BASEC within 7 working days of it becoming known.

In this category C clinical trial, a diagnostic radiopharmaceutical is used. No therapeutic products that emit ionising radiation will be used.

# STATISTICAL METHODS

## Hypothesis

**Step 1: Hypotheses**

Null Hypothesis –The new tracer is inferior to the old tracer with respect to the detection of patients with pathological PSMA-positive findings using a non-inferiority margin of -10%, i.e.

Pr(PSMA+)new – Pr(PSMA+)old < -10%

Alternative Hypothesis – The new tracer is non-inferior to the old tracer with respect to the detection of patients with pathological PSMA-positive findings using a non-inferiority margin of -10%, i.e.

Pr(PSMA+)new – Pr(PSMA+)old > -10%

## Determination of Sample Size

Power was determined using Monte Carlo simulations with 1000 repetitions and the following assumptions:

- Marginal probabilities: 80% of the patients are positive for tracer A and 80% are positive for tracer B
- Both tracers are applied to each patient
- Non-inferiority design with a one-sided alpha of 2.5%
- Non-inferiority margin of -10% (clinically acceptable margin in detection rate, balanced against the requirements for clinically realistic number of patients). We justify this margin as being less than 50% of the margin reported for superiority (22%) in a prospective trial published for ^68^Ga-PSMA-11 versus the first-generation tracer ^18^F-Choline [22].
- Non-inferiority is concluded if the lower limit of a 95% confidence interval (Wald with Bonett–Price Laplace adjustment) for the difference in the proportion of tracer-positive patients (new tracer – old tracer) is larger than the non-inferiority margin
- A pragmatic assumption is made regarding the correlation of the paired measurements. Limited data are available for this, given the dearth of comparative studies. Neither retrospective analyses [28] nor limited pilot studies [17, 27] have demonstrated any difference in detection rate. We take a worst-case scenario, and assume that both tracers are positive for 75% of the patients.

Data was simulated using function rmvbin from R package bindata [29]. With 100 patients we will have a power of 85% to detect non-inferiority.

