### Primary Analysis

The primary outcome (proportion of patients with PSMA-positive pathological lesions) will be compared between tracers using an absolute risk difference (new tracer minus old tracer) with a one-sided lower 95% confidence interval (CI) for paired proportions (Wald with Bonett–Price Laplace adjustment). If the lower limit lies above -10%, we will claim non-inferiority. Proportion of pathologic scans will be based on majority consensus reads.

The number of PSMA-positive lesions defined as pathological, benign and uncertain in each region will be analysed using separate mixed-effects Poisson regression models with tracer as fixed covariate and nested random effects for patient and region. We will report incidence rate ratios with 95% CI and p-values. As a sensitivity analysis we will compare the number over all regions using the Wilcoxon signed-rank tests and the Mann-Whitney statistic with 95% CI.

Inter-reader reliability will be analysed on the region-level based on the number of benign, pathological and uncertain lesions determined by each reader. We will calculate Krippendorff’s alpha with a ratio difference function and bootstrap 95% CI separately for each tracer.

Lesion-based PPV will be calculated for each tracer as the proportion of pathological lesions confirmed pathological during follow-up among all lesions with a known state and will be presented with 95% Wilson score CI. Using all lesions with a confirmed status during follow-up, the two tracers will be compared using McNemar’s test and an absolute risk difference with 95% confidence interval.

The semi-quantitative tumour to background ratio will be summarized on a region-level (i.e. using the mean over all positive lesions per region) and analysed using a linear mixed-effects regression model with tracer as fixed covariate and patient and region as nested random effects. The mean difference with 95% CI will be reported.

For the subset of patients with additional parametric imaging data (N=10) the planned analysis of parametric imaging parameters (see first secondary endpoint) is planned prior to completion of the study. This exploratory analysis of this secondary endpoint will not assess the primary endpoint and will not influence further trial conduct or further trial process.

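### The Bonett–Price lower limit does not hold the stated one-sided 2.5% error at the -10% margin when few pairs are discordant

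*Protocol*

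**What the plan says.** Section 11.2 fixes the design and the decision rule: "Non-inferiority design with a one-sided alpha of 2.5" per cent, a margin of -10%, and "Non-inferiority is concluded if the lower limit of a 95% confidence interval" exceeds that margin. The interval is the Wald interval for paired proportions with the Bonett–Price Laplace adjustment. The synopsis entry on the number of participants gives the same level and method.

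The power assumptions are "80% of the patients are positive for tracer A and 80% are positive for tracer B", and "We take a worst-case scenario, and assume that both tracers are positive for 75% of the patients". The result is "With 100 patients we will have a power of 85% to detect non-inferiority", from 1000 simulated trials. The simulation is described for power only; section 11.2 reports no check of the error rate at a true difference of -10%.

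Section 11.4.2 applies the same interval to the primary outcome: "If the lower limit lies above -10%, we will claim non-inferiority". There, and in the synopsis entry on statistical considerations, the limit is a one-sided 95% bound. That corresponds to an alpha of 5%, not 2.5%.

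**The concern.** A Wald-type limit uses a variance estimated from the observed discordant pairs. When discordant pairs are few and the true difference sits at the margin, samples with a favourable difference also tend to have a small estimated variance. The limit then clears the margin too often. The plan expects few discordant pairs: 10% in total under its own assumptions.

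This is the only primary decision rule. Its type I error is the chance of accepting a tracer that finds disease in 10 points fewer patients. If that chance exceeds the declared 2.5%, a non-inferiority claim carries more risk than stated, and part of the stated power is bought with the excess.

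**Working it through.** **Inputs.** From section 11.2: n = 100 pairs, margin -0.10, one-sided 2.5% (z = 1.960), 80% positive on each tracer, 75% positive on both. Hence new-only positives are 80 − 75 = 5%, old-only positives are 80 − 75 = 5%, and discordance is 10%. Section 7.4.2 replaces patients who leave before the second scan, so 100 complete pairs are assumed.

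**Rule.** Let b be the number of new-only and c the number of old-only positives. With p1 = (b+1)/(n+2), p2 = (c+1)/(n+2) and d = p1 − p2, the lower limit is

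L = d − z·√[(p1 + p2 − d²)/(n+2)],

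and non-inferiority is claimed if L > −0.10. Probabilities are summed exactly over the trinomial distribution of (b, c, concordant).

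**The plan's own figure.** At 5%/5% and z = 1.960 the power is 86.5%. The stated 85% came from 1000 repetitions, with a Monte Carlo standard error of √(0.85·0.15/1000) = 1.1 points, so it reproduces. With z = 1.645 the power would be 92.0%, so the sample size was evidently computed at one-sided 2.5%.

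**Error at a true difference of -10%, n = 100, nominal 2.5%:**

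| New-only / old-only | Discordance | Bonett–Price | Unadjusted Wald | Tango score |
|---|---|---|---|---|
| 0% / 10% | 10% | 5.76% | 5.76% | 2.37% |
| 1% / 11% | 12% | 4.21% | 4.21% | 2.04% |
| 2% / 12% | 14% | 3.65% | 3.68% | 2.22% |
| 3% / 13% | 16% | 3.22% | 3.38% | 2.19% |
| 5% / 15% | 20% | 2.74% | 3.22% | 2.16% |
| 10% / 20% | 30% | 2.53% | 2.96% | 2.49% |
| 15% / 25% | 40% | 2.55% | 2.62% | 2.55% |

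**Hand check of the first row.** With b = 0 and c = 5: d = −5/102 = −0.0490; standard error = √[(7/102 − 0.0024)/102] = 0.0255; L = −0.0490 − 1.96·0.0255 = −0.0990, which passes. With c = 6 the limit is −0.0588 − 1.96·0.0271 = −0.112, which fails. The rule therefore passes at c ≤ 5, and P(Bin(100, 0.10) ≤ 5) = 5.76%. The score test with b = 0 uses the variance at the margin, 100·(0.10 − 0.01) = 9. Then c = 4 gives (10 − 4)/3 = 2.00, which passes, and c = 5 gives (10 − 5)/3 = 1.67, which fails. Its error is P(Bin(100, 0.10) ≤ 4) = 2.37%.

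**Which row applies?** The plan states discordance only under equality, so two ways of carrying its assumptions to the margin were tried.

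- Keep 5% new-only positives and let old-only rise to 15%: 2.7%.
- Keep the plan's correlation, phi = (0.75 − 0.80·0.80)/0.16 = 0.6875. For 80% versus 70%, both-positive = 0.56 + 0.6875·√(0.16·0.21) = 0.686. New-only is then 1.4%, old-only 11.4%, discordance 12.8%, and the error 4.0%. For 85% versus 75% it is 4.5%. For 90% versus 80% the correlation is capped at zero new-only positives, and the error is 5.8%.

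**Score limit.** Over discordance from 10% to 59% its error is at most about 2.6%. Its power at the plan's alternative is 81.7% with 100 patients and 85.7% with 110.

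**The case against.** A reader might take 5.8% as the error at the plan's own 10% discordance. The documents do not support that. The plan's 10% is 5% in each direction with equal tracers. At a true difference of -10%, a discordance of 10% is the smallest possible and requires that no patient is positive only on the new tracer. The design makes that unlikely. Section 6.1.2.2 gives each tracer its own three readers, so reader variation alone should produce discordance both ways, and section 3.1 expects the new tracer to help near the bladder wall. This stands: 5.8% is a ceiling.

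A reader might also blame the Laplace adjustment, because it pulls the estimate toward zero and away from the margin. The unadjusted Wald limit has the same or a higher error in every row, so the adjustment leaves the error unchanged or lowers it. The fault lies in the Wald form.

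The 5.8% also rests on a single discrete step, five old-only positives against four. That is true, but the score limit faces the same discrete data and holds 2.4% there.

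The conflict over the level is arguably the larger problem. With z = 1.645 the error at 5%/15% is 5.7%, not 2.7%, and at 10%/20% it is 5.3%, not 2.5%. That conflict has to be settled first, but settling it at 2.5% does not remove the excess at low discordance. At 0%/10% the rule passes at c ≤ 5 with either z.

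Finally, the plan names its interval consistently, its power reproduces, and in plausible settings the excess is modest. That limits the weight of the point, but the declared error rate is still not the one that the rule delivers.

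**Conclusion.** The point holds. With 100 complete pairs and z = 1.96, the primary decision rule exceeds its stated one-sided 2.5% at low discordance. The error is about 2.7% if the plan's new-only rate is kept, about 4.0% if its correlation is carried over to 80% versus 70%, and at most 5.8% with no new-only positives. From 10%/20% upward it is about 2.5%. How much applies depends on the discordance at the margin, which the protocol does not state. The power calculation itself is sound for the rule as written. The defect is that the rule does not have the error rate attached to it.

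**What to change.** First reconcile the level: one-sided 2.5% in section 11.2 and the synopsis sample-size entry, against the one-sided 95% bound in section 11.4.2 and the synopsis statistical entry. The sample size was built on 2.5%.

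Then state in sections 11.2 and 11.4.2 and in the synopsis that non-inferiority is decided on the paired score (Tango) lower limit at one-sided 2.5%. Keep the Bonett–Price interval as a supportive display.

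Restate power as about 82% with 100 patients under the same assumptions. The cost is one sentence in each place and about 3 points of stated power (85% to about 82%). No extra patients are needed if that is accepted; keeping 85% would take about 110. Scans, readings and data collection do not change.

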| **Number of Participants with Rationale:** | Recruitment will be open until 100 patients have been recruited.  Assuming that 80% of the patients are positive for each one of the tracers and that 75% of the patients will be positive for both tracers, recruitment of 100 patients will give a power of 85% to detect non-inferiority with a non-inferiority margin of -10% and a one-sided alpha of 2.5% using the Wald confidence interval for paired proportions with the Wald Bonett-Price Laplace adjustment. |
| **Study Duration:** | 2 years |
| **Study Schedule:** | First patient examination: June (planned) 2022*  Last patient examination: June 2023*  Follow-up of 6 months (until end of Dec 23)*  Data analysis and publication within 6 months (until June 2024)*  * See additional text in Section “Study Schedule” |
| **Investigator(s):** | Sponsor: [name]. med. [name]  Principal Investigator: [name]. med. [name]  Klinik für Nuklearmedizin, Inselspital Bern  [name]  [name]  [contact]  [contact] |
| **Study Centre(s):** | Single-centre (University Clinic for Nuclear Medicine, Inselspital Bern) |

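### Section 11.2 calls 75% joint positivity a worst case, but 85% power holds at that value only and falls steeply under weaker agreement between the tracers

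*Protocol*

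**What the plan says.** Section 11.2 of the protocol (Determination of Sample Size) fixes the marginals: "Marginal probabilities: 80% of the patients are positive for tracer A and 80% are positive for tracer B". It sets a one-sided alpha of 2.5% and a margin of -10 percentage points. The decision rule is introduced as follows: "Non-inferiority is concluded if the lower limit of a 95% confidence interval (Wald with Bonett–Price Laplace adjustment"), with the lower limit to exceed the margin.

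On the dependence between the two scans, the section calls its choice pragmatic and concedes that few data exist. It notes that earlier retrospective and pilot work found no difference in detection rate. It then states: "We take a worst-case scenario, and assume that both tracers are positive for 75% of the patients". The section concludes: "With 100 patients we will have a power of 85% to detect non-inferiority".

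The study synopsis gives the same 80% and 75% assumptions and the same power, without the worst-case label. Neither place reports an observed agreement or discordance rate, or shows how power varies with joint positivity.

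**The concern.** In a paired comparison of proportions, the variance of the difference comes from the discordant patients. Fewer patients positive on both tracers, at fixed marginals, means more discordance, a wider interval and less power. A worst case for power is therefore a low joint positivity, and 75% is close to the 80% maximum.

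The support offered does not reach the assumption. Equal detection rates are a statement about the marginals. Two tracers can each be positive in 80% of patients at any joint positivity from 60% to 80%, so the absence of a difference in earlier studies says nothing about discordance.

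What is at stake is interpretation. The label presents 85% as the least power the trial could have under the assumed marginals. If non-inferiority is not shown, a reader relying on that label would discount low power as an explanation, although power depends strongly on an input for which the protocol gives no data.

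**Working it through.** **Inputs, all from Section 11.2.** Marginals 80% and 80%, so the true difference is 0; joint positivity 75%; margin -0.10; one-sided alpha 2.5% (z = 1.96); Bonett–Price adjusted Wald limit; n = 100 pairs. Section 7.4.2 replaces patients who withdraw before the second scan, so 100 complete pairs are taken as given.

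**Possible range of joint positivity p11.**
- Minimum: max(0, 0.80 plus 0.80 minus 1) = 0.60.
- Maximum: 0.80.
- Independence: 0.80 × 0.80 = 0.64.

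**What 75% implies.**
- Each discordant cell: 0.80 minus 0.75 = 0.05, so 10% discordant in total.
- Both negative: 1 minus 0.75 minus 0.10 = 0.15.
- Correlation: (0.75 minus 0.64) ÷ (0.80 × 0.20) = 0.11 ÷ 0.16 = 0.69.

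**Why discordance drives power.** With no true difference, the unadjusted standard error is √[2 × (0.80 minus p11) ÷ 100].
- At 75%: √(0.10 ÷ 100) = 0.0316. Approximate power is Φ(0.10 ÷ 0.0316 minus 1.96) = Φ(1.20) = 88.5%.
- At 64%: √(0.32 ÷ 100) = 0.0566. Approximate power is Φ(0.10 ÷ 0.0566 minus 1.96) = Φ(-0.19) = 42%.

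**Reproducing the stated figure.** Let x and y be the discordant counts (new tracer only, old tracer only). The adjusted proportions are a = (x+1)/(n+2) and b = (y+1)/(n+2), with d = a - b. The lower limit is d - 1.96 √[(a + b - d²)/(n+2)], and non-inferiority is declared when it exceeds -0.10. Summing the multinomial probabilities of all qualifying outcomes, with cells of 0.75 (both positive), 0.05 and 0.05 (discordant) and 0.15 (both negative), gives 86.5%. One million simulated trials also give 86.5%. The protocol used 1000 repetitions, for which the simulation standard error is √(0.865 × 0.135 ÷ 1000) = 1.1 points. The stated 85% therefore reproduces.

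**Power by joint positivity** (same exact calculation, n = 100, marginals 80% and 80%):

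| Positive on both | Discordant | Correlation | Power |
| --- | --- | --- | --- |
| 78% | 4% | 0.88 | 99% |
| 76% | 8% | 0.75 | 92% |
| 75% (protocol) | 10% | 0.69 | 86.5% |
| 74% | 12% | 0.63 | 80% |
| 73% | 14% | 0.56 | 74% |
| 72% | 16% | 0.50 | 69% |
| 71% | 18% | 0.44 | 64% |
| 70% | 20% | 0.38 | 59% |
| 68% | 24% | 0.25 | 52% |
| 64% (independence) | 32% | 0.00 | 42% |

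A drop of three points in joint positivity, from 75% to 72%, costs about 18 points of power (86.5% to 69%).

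**The case against.** The best defence is that a planning worst case means the worst plausible case, not the logical minimum. Both tracers bind the same target, are given to the same patient 2 days to 2 weeks apart, and no change of treatment is allowed between scans. Strong agreement is to be expected, and the primary endpoint uses a three-reader majority, which dampens single-reader noise. The protocol also admits that the assumption is pragmatic and data are limited, and the synopsis states the power conditionally.

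Much of this stands. A reader might infer that 75% is optimistic and that the trial is really powered at some much lower figure. The documents do not support that, because they contain no agreement data in either direction. A reader might also take the logical minimum of 60%, where power is 35%, as the true worst case. That would require no patient to be negative on both tracers and a correlation of -0.25. Anything below 64% is agreement worse than chance, which is not credible for two ligands of one target. Independence, at 42%, is already a severe lower reference, and the nearest departures (71% to 74%) leave 64% to 80% power.

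The defence does not rescue the label. Expecting strong agreement is not evidence that 75% is the lowest plausible value, and no figure is offered to show it. Some features of the protocol point towards more discordance: a separate reader panel for each tracer (Section 6.1.2) and the reported higher non-prostatic uptake with the new tracer (Section 3.4). They do not quantify it, but they make it hard to treat 10% as a ceiling.

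**Conclusion.** The point holds as a mislabelled and unsupported assumption, not as an arithmetic error. The 85% is right for its stated inputs. It is not a lower bound: under the same marginals, power runs from 80% at 74% joint positivity to 42% at independence, and up to 99% at 78%. The label is contradicted by the protocol's own inputs.

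The figures assume no true difference, 80% positive on each tracer, 100 complete pairs and the one-sided 2.5% level of Section 11.2. Section 11.4.2 describes a one-sided lower 95% limit. If that were applied at one-sided 5%, power would be 92% at 75% joint positivity, 72% at 70% and 55% at 64%. The levels shift, but the dependence on agreement, and so the conclusion, does not. Nothing here shows that the trial is underpowered or that 100 patients is the wrong number.

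**What to change.** In Section 11.2, delete the worst-case wording and describe 75% joint positivity as the base-case assumption, stating that it means 10% discordant patients. Give 85% as the power at that value only. Add a short table of power over a plausible range, for example 64% to 78% joint positivity, so that values on both sides of 75% are visible. If any agreement data support 75%, cite them there. The synopsis is already conditional and needs only to stay consistent with the revised section.

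The cost is a few words and one small table, and the power statement becomes less favourable. The sample size of 100, the margin, the decision rule and the analysis do not change.
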